#### The Edinburgh Postpartum Depression Rating Scale

This 10-item scale has been designed to detect depression from 6 weeks after delivery. The Edinburgh Scale scores vary between 0 and 30 with cutoff point 12 and above to detect postpartum depression [39]. Psychometric evaluation of the Farsi version of this scale is carried out in 2015 [40]. The Cronbach’s alpha for the Edinburgh Scale has been reported as 0.7. Validity of the Edinburgh Beck Scale has been reported as 0.44. The findings of the study confirmed the high validity of the Farsi version of the Edinburgh Scale for the diagnosis of postpartum depression [40].

#### The Sexual Quality of Life-Female (SQOL-F)

It is a short tool that specifically assesses the relationship between sexual function and women’s quality of life. It has been developed by Symonds et al. [41]. This 18-item questionnaire focuses on sexual self-esteem, emotional affairs, and relationships. Each item is responded with a Likert scale of strongly agree (score 6) to strongly disagree (score 1). Higher scores indicate better quality of sexual life for women [41]. Validity and reliability of the Farsi version of this scale have been confirmed by Maasoumi et al. [42].

### Primary outcome

Primary outcome of this study is to investigate changes of sexual function using the FSFI.

### Secondary outcome

The secondary endpoint is investigating the quality of women’s sexual life, which will be assessed using the Sexual Quality of Life Questionnaire. Any harm or side effects will be also reported.

### Study procedure

After obtaining the necessary permissions from the Ethics Committee of Qazvin University of Medical Sciences, registration at the Iranian Clinical Trial Registration Center (IRCT), and obtaining the permission from Qazvin Nursing and Midwifery School, the researcher will attend for recruitment in Qazvin Health Centers. The lactating women of each center will be invited for participation. The process and purpose of the research will be explained to those who meet the inclusion criteria. Also, they will be ensured that their information will be kept confidential and that the questionnaires will be anonymous and coded in accordance with the research ethics. They will enter into the study after signing the written consent form. The researcher will ensure that they can leave the study at any time. After enrolling eligible individuals, a simple block randomization will be used. Participants will be randomly assigned to the intervention and control groups.

The questionnaires will be filled out by the participants before the intervention. Then, the intervention (acupressure) will be performed as mentioned above. Evaluation of sexual function in both the intervention and control groups will be performed using the FSFI questionnaire immediately, 1 and 2 months after the intervention. Figure 3 provides the timeline of recruitment, allocation, and assessment.

**Fig. 3 Fig3:**
[figure not shown]
Schedule of enrolment, interventions, and assessments

### Statistical analysis

Data will be analyzed using the chi-square test, Fisher exact test, and independent *t* test via the SPSS v.24 software. The Kolmogorov-Smirnov and Shapiro tests will also be used to check for the normal distribution of sexual function scores. Descriptive statistics (number, mean, and standard deviation) will be used to describe the demographic characteristics of the participants. The repeated measure ANOVA will be used to compare the mean sexual function of women before and after the intervention. The significance level of all tests is set as *p* < 0.05.

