**Methods/design:**

This is a randomized clinical trial with a parallel sham control group. In this study, 76 lactating women between 6 months and 1 year after childbirth were referred to health care centers in Qazvin City and would be invited to participate. Participants will be divided into intervention (*n* = 38) and control (*n* = 38) groups using simple block randomization. Both intervention and sham control groups will be visited over 10 sessions within a 4-day interval. At each visit, the adhesives containing *Vaccaria* seed will be adhered for the intervention group, while non-latex-based adhesives with no *Vaccaria* seeds will be placed on the same ear acupoints for the sham control group. Selected ear acupoints include genitalia (two ear points), pelvic point, master shoulder, and posterior pituitary gland. The women will be asked to hold the seeds on their ears for 3 days and press each ear point three times a day for 20 s. After 3 days, they will be asked to remove the seeds from their ears and rest for 1 day. Sexual function as primary outcome in both groups will be assessed using the Female Sexual Function Index before and immediately after 1 and 2 months after the intervention. Also, Sexual Quality of Life as secondary outcome will be assessed using Sexual Quality of Life-Female (SQOL-F) before and 2 months after intervention. Data will be analyzed using repeated measure ANOVA at the significant level of 0.05.

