### Sample size calculation

Sample size is estimated according to the study of Bokaie et al. with the mean and standard deviation of total sexual function score has been reported as 24.65 ± 3.47 and 22.27 ± 3.03 in the intervention (telephone counseling group) and control groups, respectively [30]. Therefore, considering the first type error (α) = 0.05 (95% confidence), the second type error (β) = 0.2 (80% power) and error *d* = 5, and the possibility of 10% loss to follow-up, 38 individuals for each group are required. So, the total sample size will be 76 people.

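### The Methods name no analysis for SQOL-F, and adjusting for the baseline SQOL-F already collected would be more efficient than either test the article could imply

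*Protocol article*

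**What the plan says.** The abstract (Methods/design) gives the secondary endpoint and its schedule: "Sexual Quality of Life as secondary outcome will be assessed using Sexual Quality of Life-Female (SQOL-F) before and 2 months after intervention". The next sentence is general and names no endpoint: "Data will be analyzed using repeated measure ANOVA at the significant level of 0.05". Coming straight after both outcomes, it reads most naturally as covering both.

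The Statistical analysis section opens with "Data will be analyzed using the chi-square test, Fisher exact test, and independent *t* test via the SPSS v.24 software" and does not say which variables these three tests are for. It then ties repeated-measures ANOVA to the FSFI: "The repeated measure ANOVA will be used to compare the mean sexual function of women before and after the intervention". The planned normality checks are also described for sexual function scores only. SQOL-F is not mentioned in this section.

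The Secondary outcome section names the endpoint without a test: "The secondary endpoint is investigating the quality of women’s sexual life, which will be assessed using the Sexual Quality of Life Questionnaire". The article nowhere mentions adjustment for baseline.

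**The concern.** The abstract's statement of method is broader than the section it summarises, so a reader of the Methods cannot tell how the one named secondary efficacy endpoint will be compared between arms. The article suggests two candidates: repeated-measures ANOVA, if the abstract is taken at face value, and the independent t test, if one looks for what else the Statistical analysis section lists for a continuous score.

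As usually run, neither makes the best use of the SQOL-F baseline. In a trial of 76 women, with no sample-size calculation for SQOL-F, precision on this endpoint is worth having. What is at stake is the power and the width of the confidence interval for the secondary endpoint. The primary result is not affected.

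**Working it through.** **Inputs from the article.** 38 women per arm and 10% expected loss (Sample size calculation); SQOL-F at baseline and 2 months (abstract); level 0.05 (Statistical analysis), taken here as two-sided. The two-visit SQOL-F schedule comes from the abstract, because Study procedure gives follow-up times for FSFI only and the schedule figure is not shown.

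**The plan's own figure.** It concerns FSFI. From "the mean and standard deviation of total sexual function score has been reported as 24.65 ± 3.47 and 22.27 ± 3.03" the difference is 24.65 − 22.27 = 2.38. With SD 3.47 in both arms, two-sided 0.05 and 80% power:

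n = 2 × (1.96 + 0.84)² × 3.47² / 2.38² ≈ 33.4, so 34 per arm; 34 / 0.9 = 37.8, so 38.

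The stated 38 is reproduced on that choice of SD. There is no corresponding figure for SQOL-F. The only number carried forward is the expected completers: 38 × 0.9 = 34.2, taken as 34 per arm.

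**Assumptions.** The article gives no SQOL-F effect, SD or baseline-to-follow-up correlation. I take equal SDs, normal scores, a true 2-month difference of 0.6 SD, and r = 0.3, 0.5 and 0.7.

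**Variance of each estimator of the arm difference**, relative to the unadjusted 2-month comparison:

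- t test on the 2-month score: 1.
- Arm-by-time test of repeated-measures ANOVA. With two time points this is the t test on change: 2(1 − r).
- ANCOVA with arm and baseline SQOL-F: 1 − r².

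Since 1 − r² = (1 − r)(1 + r), it is below 2(1 − r) whenever 1 + r < 2, that is r < 1. It is below 1 whenever r is not zero. So ANCOVA has the smallest variance for every r strictly between 0 and 1.

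**Expected test statistic**, 0.6 × √(34/2) / √(variance factor), where 0.6 × √17 = 2.474, **and power** from 20,000 simulated trials per setting:

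| r | Analysis | Variance factor | Expected statistic | Power |
|---|---|---|---|---|
| 0.3 | 2-month t test | 1.00 | 2.47 | 69% |
| 0.3 | Change (arm by time) | 1.40 | 2.09 | 55% |
| 0.3 | ANCOVA | 0.91 | 2.59 | 72% |
| 0.5 | 2-month t test | 1.00 | 2.47 | 68% |
| 0.5 | Change (arm by time) | 1.00 | 2.47 | 68% |
| 0.5 | ANCOVA | 0.75 | 2.86 | 80% |
| 0.7 | 2-month t test | 1.00 | 2.47 | 68% |
| 0.7 | Change (arm by time) | 0.60 | 3.19 | 88% |
| 0.7 | ANCOVA | 0.51 | 3.46 | 93% |

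**Second effect size.** At 0.5 SD, with 40,000 trials per setting, power at r = 0.3, 0.5 and 0.7 is 40, 53 and 75% for change, 53% throughout for the 2-month t test, and 56, 64 and 80% for ANCOVA. The ordering is the same.

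**Against the repeated-measures reading alone**, the ratio of ANCOVA variance to change variance is (1 + r)/2 = 0.65, 0.75 and 0.85. The gain shrinks as r rises.

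**The case against.** **A direct contradiction?** A reader might infer that the article prescribes two conflicting analyses for SQOL-F: repeated-measures ANOVA in the abstract and an unadjusted t test in the Methods. The text does not support this. The t test is listed beside the chi-square and Fisher exact tests with no variable assigned, and those three are the usual set for comparing baseline characteristics. Even if a t test were meant for SQOL-F, it could be on change, which would equal the arm-by-time test. Nor does the Statistical analysis section say that repeated-measures ANOVA is for sexual function only. What stands is a difference in scope that leaves SQOL-F unnamed.

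**An inflated false-positive rate?** With no true effect, at least one of the 2-month t test and the change test is significant in about 9% of simulated trials. A reader might take this as nearly doubling the stated 5%. It would require both tests to be run and the favourable one reported, and the article assigns SQOL-F no such pair. The claim cannot be laid against this plan.

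**Silence in a condensed article?** The exact secondary-endpoint model may sit in a document not shown, so its absence is no fault by itself. That is fair. The mismatch between abstract and Methods is still in this text and can be settled only here.

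**A mere preference for ANCOVA?** Repeated-measures ANOVA is valid in a randomised two-arm trial and does use the baseline, through the arm-by-time term. Lower efficiency is not an error, no power is claimed for SQOL-F, and at r = 0.7 the gain is modest (88% to 93% at 0.6 SD). All of this stands, and it is why the point is an improvement and not a correction of a mistake.

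**Conclusion.** The point holds as a free improvement. The abstract's repeated-measures statement is wider than the Statistical analysis section, which names no SQOL-F test. Both analyses the article could be read as implying are less efficient than adjusting for baseline SQOL-F.

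That ordering is algebraic for any r between 0 and 1 under equal variances. Its size rests on assumed values. At 34 per arm and 0.6 SD, ANCOVA adds about 17, 12 and 5 percentage points of power over the change test at r = 0.3, 0.5 and 0.7. Over the 2-month t test it adds about 3, 12 and 25 points (72 − 69, 80 − 68, 93 − 68). Which of the two implied tests loses more therefore depends on r, which the article does not give; ANCOVA avoids having to guess.

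Neither a contradiction between two stated SQOL-F analyses nor an inflated error rate is established.

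**What to change.** In the Statistical analysis section, add one sentence: the 2-month SQOL-F total is compared between arms by ANCOVA with arm and baseline SQOL-F as terms, reporting the adjusted mean difference with its 95% confidence interval. In the abstract, limit the repeated-measures ANOVA sentence to the FSFI and name ANCOVA for SQOL-F, so that the two places agree.

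The cost is two sentences of text and one degree of freedom. Baseline SQOL-F is already collected, no extra visits or data are needed, and SPSS fits the model. The change should be made before anyone sees outcome data by arm.

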## Background

The post-childbearing period is a crucial stage in the woman’s life that involves physical, hormonal, mental, social, and cultural changes [1]. Fatigue, insomnia, some stressors such as child care, and changes in the body image along with hormonal changes can reduce interest in sexual life and decrease the number of sexual intercourses during this period [1]. Endocrine function of lactation has a negative effect on sexual function, because prolactin decreases sexual hormones such as androgen and estrogen. This mechanism reduces sexual function because of vaginal dryness, vaginal epithelium atrophy, and dyspareunia [2]. About two thirds of women during lactating period experience at least one sexual problem, such as decreased libido, lack of sexual pleasure, dyspareunia, and vaginal dryness, which usually are resolved within 1 year after childbirth [3, 4]. The prevalence of sexual dysfunction increases from 19 to 63% in the prepartum period [5] to 34 to 91% in the postpartum period [6]. The results of various Iranian studies confirmed the high prevalence (31.5 to 85.4%) of sexual dysfunction during lactation [7, 8]. Therefore, sexual dysfunction is a common problem during lactation that needs more attention from health care providers.

In the post-childbearing period, most women try to return to their sexual life within 8 to 12 weeks after childbirth. However, it may take up to 1 year to resume sexual relationships with the same quality of before pregnancy [9]. Psychotherapy and pharmacotherapy are two main methods for treating female sexual dysfunction (FSD) [10]. However, the US Food and Drug Administration (FDA) does not recommend any foods or medicines for the treatment of FSD [11]. Therefore, non-pharmacological therapies such as complementary medicine are a potentially safer alternative to pharmacological therapy. Acupressure is one of the non-invasive complementary methods of traditional Chinese medicine (TCM) based on the principles of acupuncture [12]. Acupuncture stimulates medical points and meridians that are distributed throughout the body to regulate physiologic reactions [13]. Acupressure, like acupuncture, modulates a person’s vital energy by stimulating acupoints and meridians that are distributed throughout the body [14].

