### Research aim

This study is designed to investigate the effect of ear acupressure on the sexual function of lactating women.

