## Methods

### Design and setting

This is a randomized clinical trial with a parallel sham controlled group. The study is designed in accordance with the CONSORT standards. Lactating women referred to health care centers in Qazvin City, Iran, will be invited to participate. Figure 1 shows the CONSORT flow diagram. The current protocol is organized based on the SPIRIT-TCM extension [29].

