### Participants

In this study, breastfeeding women between 6 months and 1 year after childbirth will be referred to health care centers in Qazvin City, Iran, and they will be invited to participate in the study. Inclusion criteria will be willingness to participate in the study, being literate, being primiparous, breastfeeding, full-term singleton delivery, lesion-free auricle, no ulcer and pain in the ear, and ability to present for all intervention sessions. Exclusion criteria will be being away from their spouse for more than 1 month, having complications during pregnancy, or having postpartum depression in the post-childbearing period. These criteria were diagnosed using the Edinburgh Postpartum Depression Scale, substance abuse in the individual or the spouse, and history of illnesses affecting sexual function in a woman or her spouse (e.g., premature ejaculation, cardiovascular, mental health disorders, thyroid diseases, any form of cancer, or injuries of the genital area). The use of drugs affecting sexual function such as psychotropic, cardiovascular, neurological, and hormonal drugs will also be excluded. After the initial screening, the Demographic and Obstetric Questionnaire and Female Sexual Function Index (FSFI) will be completed by the participants before any intervention.

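### The FSFI repeated-measures ANOVA is specified only as a before-versus-after comparison and names no between-arm contrast, so a significant result as worded could reflect postpartum recovery rather than acupressure.

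*Protocol article*

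**What the plan says.** The Statistical analysis section gives one sentence on how the repeated FSFI scores are compared: "The repeated measure ANOVA will be used to compare the mean sexual function of women before and after the intervention". The abstract repeats the method without a contrast: "Data will be analyzed using repeated measure ANOVA at the significant level of 0.05". The Primary outcome section adds neither a comparator nor a time point: "Primary outcome of this study is to investigate changes of sexual function using the FSFI".

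The Statistical analysis section also opens with "Data will be analyzed using the chi-square test, Fisher exact test, and independent" *t* test. None of these tests is assigned to an outcome.

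The design is comparative. Under Design and setting: "This is a randomized clinical trial with a parallel sham controlled group". The sample size section starts from two group means, 24.65 (SD 3.47) and 22.27 (SD 3.03). Under Study procedure, FSFI is taken in both groups at baseline, immediately after the intervention, and 1 and 2 months later.

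Two other statements bear on the time course. The Background says of sexual problems in lactation: "which usually are resolved within 1 year after childbirth". The Participants section recruits "breastfeeding women between 6 months and 1 year after childbirth".

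**The concern.** The stated aim is causal: "This study is designed to investigate the effect of ear acupressure on the sexual function of lactating women". In a sham-controlled trial, that effect is the difference between arms. A before-versus-after comparison measures how FSFI moves over time, whatever the cause.

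The document itself gives a reason to expect movement without treatment. Ten sessions at 4-day intervals take about 40 days, and two months of follow-up bring the total to about 100 days. Much of this falls in the period when, by the Background, problems are resolving. Both arms also receive the same sessions, so non-specific improvement is possible in both. The sham arm is there to subtract this, and the sentence as written does not use it.

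At stake is the trial's main efficacy claim. A small p-value for time could be reported as an effect of acupressure when the arms do not differ.

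**Working it through.** **1. Which contrast was the trial sized for?** Inputs from the sample size section: difference 24.65 − 22.27 = 2.38, α = 0.05 (taken as two-sided), 80% power, 10% loss. With SD 3.47 in both arms, n = 2 × (1.960 + 0.842)² × 3.47² / 2.38² = 33.4, so 34 per arm; 34 / 0.9 = 37.8, so 38. This reproduces the stated 38 per group as a two-arm comparison of means. (The pooled SD of 3.26 gives 30, or 34 after loss.) The trial is sized on one contrast and the analysis sentence states another.

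**2. How often is the time effect significant when treatment does nothing?** Assumptions: n = 34 completers per arm; four visits; σ² = (3.47² + 3.03²)/2 = 10.61 (SD 3.26); equal correlation ρ between visits of 0.3, 0.5 or 0.7; the same recovery of *r* points in both arms. The correlations and *r* are not in the document.

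The time F test has 3 and 3(2n − 2) = 198 degrees of freedom, with noncentrality

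λ = 2n × Σ(m_k − m̄)² / [σ²(1 − ρ)].

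The sum is 0.5556 r² if recovery is linear over the four visits, and 0.75 r² if it is complete by the first post-intervention visit (step). Example: r = 1, ρ = 0.5, linear: λ = 68 × 0.5556 / (10.61 × 0.5) = 7.12, giving 59%.

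| Common recovery | Linear, ρ = 0.3 / 0.5 / 0.7 | Step, ρ = 0.3 / 0.5 / 0.7 |
|---|---|---|
| 0.5 points | 13% / 17% / 27% | 17% / 22% / 35% |
| 1 point | 44% / 59% / 83% | 57% / 73% / 93% |
| 1.5 points | 81% / 93% / 99.5% | 92% / 98% / 100% |

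Common recovery cancels from any between-arm contrast. In simulation under linear recovery (2,000 trials per setting, recovery 0 to 2.38 points), the group-by-time test rejected in 4.0–6.2% of null trials, and baseline-adjusted ANCOVA at 2 months in 4.0–5.9%.

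**3. If a group factor is intended, what does each between-arm test deliver?** Take a true effect δ = 2.38, constant over the three post-intervention visits, with the same n, σ² and ρ.

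- *Group main effect.* Baseline is one of four levels and carries no effect, so the contrast is 0.75 × 2.38 = 1.785. The variance of a woman's four-visit mean is σ²(1 + 3ρ)/4. At ρ = 0.5 this is 6.63, and λ = 1.785² / (2 × 6.63/34) = 8.17.
- *Group-by-time, 3 df.* λ = (n/2) × 0.75δ² / [σ²(1 − ρ)]. At ρ = 0.5, 17 × 4.248 / 5.305 = 13.61.
- *ANCOVA on the mean of the three post scores.* Residual variance is σ²[(1 + 2ρ)/3 − ρ²]. At ρ = 0.5 this is 4.42, and λ = 2.38² / (2 × 4.42/34) = 21.8.

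| Test | Power, ρ = 0.3 / 0.5 / 0.7 |
|---|---|
| Group main effect | 0.90 / 0.80 / 0.72 |
| Group-by-time | 0.74 / 0.88 / 0.99 |
| ANCOVA on post mean | at least 0.99 throughout |

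Baseline-adjusted ANCOVA at a single named visit has residual variance σ²(1 − ρ²) and power of about 0.88 / 0.93 / 0.99. The planned 76 women are enough for either adjusted contrast.

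**The case against.** The strongest reply is that a condensed article sentence should be read in context. The design is parallel, FSFI is measured in both groups, the sample size is two-arm, and the statistician is blinded to group, which matters only if group enters the analysis. The natural reading is then a repeated-measures ANOVA with group as the between-subject factor, and its group-by-time test holds 5% whatever the recovery. The listed independent *t* test might also compare arms.

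This stands in part. A reader might infer that the plan has rejected a between-arm analysis; the text does not exclude one. But it does not name one either, and the contrast it does name is a different one. Even the generous reading leaves open whether the main effect or the interaction decides. The *t* test is tied to no outcome, so it does not settle the matter.

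A reader might also infer that natural recovery would by itself make the result significant. The document does not support this. It gives no recovery in FSFI points, entry does not require a score below the dysfunction cut-off of 28, and women enrolled near 12 months are followed past the point by which problems usually resolve. At half a point of recovery, most null trials would still be non-significant.

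Finally, the power comparison shows inefficiency rather than error. It assumes a constant effect over the three visits, which favours averaging them. At correlations of 0.5 and 0.7 the group-by-time test still exceeds the planned 80%.

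**Conclusion.** The point holds in this form: the one contrast stated for the primary outcome is before versus after, it does not match the design or the sample size, and it cannot separate acupressure from recovery. If the time effect were taken as the test, the chance of p < 0.05 with no treatment effect would be about 13–35% at 0.5 points of common recovery, 44–93% at 1 point and 81–100% at 1.5 points. These ranges rest on 34 completers per arm, SD 3.26, equal correlations of 0.3 to 0.7, equal recovery in both arms, and shapes from linear to step. The recovery size is assumed, so the supported word is *could*.

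If a group factor is intended, the group-by-time test is valid. What is then lost is efficiency and a single effect estimate: the interaction is a 3-df test, and the main effect dilutes a constant effect to 75%. Baseline adjustment is the better choice here, but not the only valid one; a prespecified group-by-time contrast would also control the type I error.

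**What to change.** Replace the sentence on the repeated-measures ANOVA with wording such as:

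*The primary analysis is the between-arm difference in post-intervention FSFI total, adjusted for baseline FSFI by ANCOVA or a linear mixed model and reported with a 95% confidence interval. Before-to-after changes within an arm are descriptive and support no claim of efficacy.*

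The text should also fix one contrast in advance: either the average of the three post-intervention visits or a single named visit. Adjusting for months since delivery, and analysing SQOL-F by ANCOVA on its baseline value, are optional.

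The cost is wording only. Baseline FSFI and delivery date are already collected, the planned software (SPSS v.24) fits these models, and no more women are needed. The change should be made before any unblinded look at the data.

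### Repeated-measures ANOVA over four FSFI assessments drops every woman with one missing score; the sample size covers the lost numbers but not the possible selection bias

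*Protocol article*

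**What the plan says.** The protocol's Statistical analysis section names one longitudinal method for the FSFI: "The repeated measure ANOVA will be used to compare the mean sexual function". The same section says the data will be analysed "via the SPSS v.24 software". The Abstract also names repeated-measures ANOVA.

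There are four assessments. Study procedure gives the baseline, "The questionnaires will be filled out by the participants before the intervention", and then follow-up "using the FSFI questionnaire immediately, 1 and 2 months after the intervention". That section also lets women leave at any time.

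Loss is expected. Sample size calculation allows for "the possibility of 10% loss to follow-up, 38 individuals for each group are required".

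The article names no mixed model and no imputation. It does not say in words that only completers will be analysed.

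**The concern.** Classical repeated-measures ANOVA, which in SPSS is the general linear model repeated-measures procedure, needs a complete row for each woman. One missing FSFI out of four removes her and the scores she did give. Four assessments, an expected loss and this method together produce a completers-only comparison.

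Randomisation protects the comparison of everyone assigned. It does not protect a comparison of those who stayed, if staying depends on how a woman is doing and does so differently in the two arms. Women who notice no benefit may be less likely to finish ten sessions and three follow-ups. The discarded scores matter as well: an early low FSFI from a woman who later leaves is the information that would let an analysis correct for her leaving.

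**Working it through.** **Inputs.** Sample size calculation gives 24.65 (SD 3.47) and 22.27 (SD 3.03), alpha 0.05, power 80%, 10% loss, and 38 per arm. Two-sided testing is assumed. Difference: 24.65 − 22.27 = 2.38. Pooled SD: √[(3.47² + 3.03²)/2] = 3.26.

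**The plan's own figure.** With the larger SD in both arms, n = 2 × [3.47 × (1.960 + 0.842)/2.38]² = 33.4, so 34 per arm, and 34/0.9 = 37.8, so 38. The stated 38 reproduces. (The pooled SD gives 30, inflated to 34. The stated error of 5, read as the difference, gives 7.) The plan therefore expects about 34 evaluable women per arm.

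**Numbers analysed at 10% total loss.** 38 × 0.9 = 34.2 per arm, about 68 of 76. About 8 randomised women, and any FSFI scores they gave, are left out. In numbers, this is what the allowance was for.

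**Power if more women are incomplete (assumption).** The protocol gives no per-visit rate. If each of the three follow-ups were missed independently:

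| Missed per visit | Complete | Per arm | Power, SD 3.26 | Power, SD 3.47 |
|---|---|---|---|---|
| 10% total, as planned | 90% | 34 | 0.84 | 0.80 |
| 5% | 0.95³ = 86% | 32.6 | 0.83 | 0.78 |
| 10% | 0.9³ = 73% | 27.7 | 0.76 | 0.71 |

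These are two-sample t-test powers for a single visit. If the effect is 2.38 at all three follow-ups, the SD of a woman's three-visit mean is 3.26 × √[(1 + 2ρ)/3]. Power for that averaged difference (SD 3.26) is then 0.95 with 34 per arm and 0.91 with 27.7 at ρ = 0.5, and 0.91 and 0.85 at ρ = 0.7.

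**Selection bias: illustration (assumptions).** Suppose there is no true effect, correlation is equal between all assessments, and the 10% of one arm with the worst change from baseline to the first follow-up leave, while loss in the other arm is unrelated to outcome.

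- Removing the lowest 10% of a normal variable raises the mean of the rest by φ(1.282)/0.9 = 0.195 SD.
- The SD of change is 3.26 × √[2(1 − ρ)]: 3.85 at ρ = 0.3 and 2.06 at ρ = 0.8.
- The shift in change at the first follow-up is 0.195 × 3.85 = 0.75, or 0.195 × 2.06 = 0.40. At each later visit it is half that.
- Averaged over the three visits, the shift is two thirds of the first: 0.50 at ρ = 0.3, 0.38 at ρ = 0.6 and 0.27 at ρ = 0.8. That is 11% to 21% of 2.38.

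**Extreme case.** If all the trial's loss is the lowest-scoring 20% of one arm at the first follow-up, completers there score φ(0.842)/0.8 × 3.26 = 1.14 points too high at that visit. At ρ = 0.3 to 0.7 the later visits are 1.14ρ = 0.34 to 0.80 too high. Their baseline is raised by the same 1.14ρ, so change from baseline is inflated by 1.14(1 − ρ) = 0.34 to 0.80 at the first follow-up and by nothing later.

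**Loss unrelated to outcome.** Expected bias is zero and only precision is lost.

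**The case against.** The strongest reply is that completers-only is inferred. The article names no analysis set and no SPSS procedure, and an analysis plan that is not shown might impute before the ANOVA. This limits the wording of the point but does not remove it. The protocol fixes the method, and that method in its standard form cannot use an incomplete row. A later plan would have to supplement or replace what is written here.

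Two stronger readings are tempting.

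- A reader might infer that the trial gives up intention to treat. The article neither promises such an analysis nor abandons it, so that goes too far.
- A reader might infer that the trial becomes underpowered. The documents do not support this either: 38 is 34 inflated for 10% loss, so on the plan's own figure the allowance already covers listwise deletion. The 73% complete and the 76% power rest on an assumed, independent 10% miss at every visit. Women who withdraw miss all later visits together, which leaves more complete cases than that. The averaged contrast stays above 80% even then.

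On bias, the documents give neither reasons for loss nor its split by arm. Similar outcome-related loss in both arms would largely cancel, and the 1.14 figure needs every lost woman to be among the lowest scorers of one arm. The protocol also takes steps against loss: ability to attend all sessions is an inclusion criterion, and women receive daily texts and telephone reminders. These points reduce the likely size. They do not justify discarding scores already collected.

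Finally, a mixed model does not cure loss that depends on scores never observed. That stands, and is why the fix includes further follow-up and a sensitivity analysis.

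**Conclusion.** The point holds as a weakness in a method the protocol fixes. As written, about 34 of 38 women per arm would be analysed at the planned 10% loss, and the scores of the others would be thrown away. Power is secondary and is affected only if incomplete cases exceed 10%.

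The main risk is selection bias. It is zero if loss is unrelated to outcome, and roughly 0.3 to 0.5 FSFI points against the 2.38 planning difference if the worst-responding 10% of one arm leave. The 1.14 at the first follow-up is an extreme case. These sizes rest on assumed correlations and assumed reasons for leaving, and on the standard SPSS procedure with no prior imputation. The change should be made because it protects the primary comparison at little cost.

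**What to change.** 1. Replace the repeated-measures ANOVA with a likelihood-based linear mixed model (SPSS MIXED): group, visit, group-by-visit and baseline FSFI, with unstructured covariance. Use all available FSFI scores of all randomised women, in the arm assigned, however many sessions they attended.
2. Seek all three follow-up FSFI assessments from women who stop the sessions, including those who stop before the first post-intervention assessment, unless they withdraw consent.
3. Report by arm the number randomised who have no post-intervention FSFI. With baseline as a covariate these women add nothing to the group contrast, and an entry rule of at least one follow-up score would hide them.
4. Give the complete-case analysis as a sensitivity analysis, with another for data not missing at random.

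The cost is a change of wording, slightly more analysis work, and some effort to reach women who have stopped. The software already named can fit the model. The model still assumes missingness at random, which item 4 is there to test.
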